## Interim analysis

Pre-planned interim analyses will be performed at one-third and two-thirds of the trial’s course (first analysis ideally estimated at 6 months after start of trial), as determined by the DSMB charter or otherwise when the DSMB requests it.

### Sample size calculation

To achieve statistically significant results (p<0.05) with a power of 90% and a true treatment difference of 1 day for the primary outcome (from 3.2 DCFDs in the placebo group to 4.2 in the haloperidol group, SD in both groups is equal to 4.2), 371 patients are needed in each group (n=742). These estimates are derived from the previous implementation study, which included 4727 patients in three 4-month periods in the same six participating ICUs and found delirium incidence of 27% (and increase of DCFDs from 60% to 70%).^33^ Consequently, presuming an informed consent rate of 40%, we need 18 months to encounter 1900 patients with a newly diagnosed delirium to include the required 742 patients. Because of estimated workload due to follow-up visits, including, for example, neurocognitive testing, we propose to select a convenience sample of two-thirds of ICU survivors (estimated around 400 of 575 survivors) as a random sample for the cognitive, functional and secondary outcome variables.

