**Trial registration:**

NCT03628391

Strengths and limitations of this studyThis study is the first sufficiently powered randomised, multi-centre, double-blind, placebo-controlled clinical trial in Europe.Extensive neurocognitive testing will be conducted with a valid test battery in order to assess cognitive impairment at 3 and 12 months after intensive care unit (ICU) admission.We will assess patient and family experiences associated with delirium as a novel outcome.There are little data on the optimal haloperidol regimen in ICU patients; the maximum haloperidol dose of 15 mg/day in our study may still be subtherapeutic.Lack of true clinical equipoise among nurses and physicians regarding the use of haloperidol may hamper motivation for the study.

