### Randomisation, blinding and treatment allocation

Legal representatives of eligible patients (when the patient is sedated or otherwise temporarily unable to consent) or the patient himself/herself will be asked for informed consent shortly after admission when the patient has no delirium or as soon as possible after admission when the patient already has delirium. Online supplemental appendix 6 contains an example of the patient consent form. In this study, the presence of delirium will be considered to be confirmed when the bedside nurse deemed the patient to have delirium based on assessment with the ICDSC or CAM-ICU, given the previous large-scale implementation project.^33^

10.1136/bmjopen-2019-036735.supp6Supplementary data

Delirious patients who fulfil all inclusion but no exclusion criteria, and for whom written informed consent has been obtained (as recorded in medical file), will be randomised. Randomisation coordination and start of a new case record form (CRF) will be guided by the electronic data capture (EDC) system of ALEA, constructed by the Clinical Trial Centre of the Erasmus Medical Centre and calibrated with the coordinating (Erasmus MC) and local pharmacies. We will randomise the recruited patients using a block design of eight patients in one block, and one block is assigned to a centre. We will have eight batches (numbered 1 through 8) of treatment and placebo, with four batches of placebo and four treatment (haloperidol). Each block will have a random assignment of eight batch numbers, having four placebo and four haloperidol patients included (a combination of 1 to 4 and 5 to 8 in random order). After eight patients are included in the study (ie, a block is full), a new block will be assigned to a centre.

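### The follow-up sample for cognition and function is called both a convenience and a random sample; only a random draw protects the comparison of arms

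*Protocol article*

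**What the plan says.** The Sample size calculation section of the protocol article explains that follow-up visits, neurocognitive testing among them, are too much work to carry out in every survivor. It then says "we propose to select a convenience sample of two-thirds of ICU survivors (estimated around 400 of 575 survivors) as a random sample", to be used "for the cognitive, functional and secondary outcome variables".

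Other parts of the article bear on this:

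- The strengths and limitations list (printed under Trial registration) counts this testing as a strength: "Extensive neurocognitive testing will be conducted with a valid test battery in order to assess cognitive impairment at 3 and 12 months".
- Randomisation, blinding and treatment allocation describes how treatment is allocated: blocks of eight per centre through ALEA, each "having four placebo and four haloperidol patients included". It does not describe how the follow-up sample is drawn. It adds that follow-up procedures obey SOPs, and that questionnaires may be sent or visits made at home.
- Statistical analysis promises an intention-to-treat analysis of all randomised participants. It plans parametric or non-parametric tests for the cognitive and functional outcomes, without reference to the sampling.
- Investigational product, and the randomisation section, state that staff, patients and families are blinded.

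**The concern.** In a random sample, chance decides who is tested. In a convenience sample, ease of access decides. The sentence names both, so a site could follow it either way.

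The choice matters because it is made among ICU survivors, after randomisation and after exposure to study drug. The stated motive is workload, and workload favours patients who are easy to reach and to test. Cognition and function plausibly influence who those patients are, so selection could depend on the outcome being measured.

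Two things are at stake. The tested group may look healthier than survivors as a whole. And if haloperidol alters recovery, and so alters who is easy to follow, the tested patients in the two arms may no longer be comparable.

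**Working it through.** **1. The plan's own figure.** Inputs from Sample size calculation: significance level 0.05, power 90%, means of 3.2 (placebo) and 4.2 (haloperidol), hence a difference of 1 day, and an SD of 4.2 in each arm. Taking the test as two-sided with 1:1 allocation:

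n per group = 2 × SD² × (1.960 + 1.282)² / difference² = 2 × 17.64 × 10.51 / 1 = 370.7, rounded up to 371, or 742 in total.

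This matches the stated size exactly. It concerns delirium and coma-free days only and does not depend on the follow-up sample.

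**2. Size of the follow-up sample.** 400/575 = 69.6%; two-thirds of 575 = 383. Between 575 − 400 = 175 and 575 − 383 = 192 survivors would not be selected.

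**3. If selection is random.** The only cost is precision. For a standardised outcome with equal arms, two-sided 0.05 and 80% power, the detectable difference is (1.960 + 0.842) × √(4/N):

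| N assessed | Calculation | Detectable difference |
|---|---|---|
| 575 | 2.802 × 0.0834 | 0.23 SD |
| 400 | 2.802 × 0.1000 | 0.28 SD |
| 383 | 2.802 × 0.1022 | 0.29 SD |

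These figures assume that every selected patient is assessed and that survivors split equally between arms.

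**4. If selection is by convenience.** The documents give no figures for this, so what follows is an illustration on assumptions. Let the outcome be standard normal among survivors in each arm, with no true treatment effect. Let 69.6% be selected in each arm, with the log-odds of selection rising by a slope b for each SD of better outcome. The mean outcome among those selected is then:

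| Slope b | Mean among selected, relative to all survivors |
|---|---|
| 0 (random) | 0 |
| 0.25 | about 0.07 SD higher |
| 0.5 | about 0.14 SD higher |
| 1.0 | about 0.26 SD higher |

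The spurious difference between arms, d, is the difference of the two means. With 200 per arm the standard error is √(4/400) = 0.10 SD, and a nominal 5% test rejects with probability Φ(d/0.10 − 1.96) + Φ(−d/0.10 − 1.96):

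| Slopes in the two arms | Spurious difference | Rejection rate |
|---|---|---|
| 0 and 0 | 0 | 5% |
| 0.5 and 0.5 | 0 | 5% |
| 0.25 and 0.5 | 0.07 SD | 11% |
| 0.5 and 1.0 | 0.11 SD | 20% |
| 0 and 0.5 | 0.14 SD | 30% |
| 0 and 1.0 | 0.26 SD | 73% |

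The second row is the important one. Selection on the outcome that works equally in both arms makes the sample look 0.14 SD healthier than survivors as a whole, yet with no true effect it creates no false difference between arms. A false difference requires selection that differs by arm. The last row is a deliberately extreme contrast.

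**The case against.** **Random may be the intended word.** That is possible. Subsampling would then cause no bias, and the repair is to delete one word and name the draw. The current text does not settle it.

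**The mechanism may be in the SOPs.** This is a condensed article, and how, when and by whom patients are drawn may be fixed in documents not shown. The absence of that detail is therefore not the point. The point is the contradiction in the rule that the article does state.

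**Blinding and home follow-up protect the comparison.** Blinding rules out deliberate choice by arm, which makes the unequal rows above less likely. It does not stop selection on patient condition, which treatment may change. Home visits and posted questionnaires help to retain patients once chosen, including incapacitated ones, but do not determine who is chosen.

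**Stronger readings that a reader might infer.**

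- *That mortality would be measured only in sampled ICU survivors*, because the sample is said to be "for the cognitive, functional and secondary outcome variables" and mortality is a secondary outcome. The documents do not support this. The sentence is motivated by follow-up visits, which mortality does not need. Taken literally it would also restrict in-ICU measures such as RASS to sampled survivors, which cannot be meant. Statistical analysis includes all randomised participants. At most, the scope wording could be tighter.
- *That about 400 is an arithmetic error for 383.* It is a loose rounding of a forecast, nothing is powered on it, and the detectable difference barely moves.
- *That a convenience sample necessarily destroys the randomised comparison.* As shown above, it does so only when selection differs by arm.

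**Conclusion.** The contradiction is real, stands in the current text and is not resolved elsewhere in the article. It should be corrected, because the affected outcomes are presented as a strength of the trial and the repair is cheap.

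Its consequence is conditional. Under random selection the loss is precision only, from 0.23 SD to about 0.28 to 0.29 SD detectable at 80% power. Under convenience selection the sample would tend to under-represent impaired survivors, and the comparison of arms could be biased if treatment changes who is easy to follow. The illustrated differences of 0.07 to 0.26 SD rest wholly on assumed selection slopes. They show what could happen and do not estimate what will happen.

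The primary outcome and its sample size are untouched. Restriction to survivors is a separate selection after randomisation, which a random draw would not remove.

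**What to change.** In Sample size calculation, delete the word convenience and state the following:

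- The two-thirds sample is drawn by computer in ALEA, stratified by centre and, within the blinded system, by arm.
- New patients are drawn at randomisation, before survival or outcome is known; those drawn who survive the ICU are followed.
- Patients already enrolled but not yet selected are drawn by computer, without reference to their condition. This transition rule is needed because recruitment began in February 2018.
- Drawn patients who prove hard to reach are not replaced.
- Selected, assessed and non-assessed survivors are reported by arm.

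Optionally, replace the reference to secondary outcome variables with the follow-up tests and questionnaires.

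The cost is a selection flag in a system already in use, a short text change and the transition rule. The expected number of visits stays about the same. Completion among drawn patients may be somewhat lower than among patients chosen for ease of access, and patients selected before the change remain as they were chosen and should be identifiable in the report.

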### Patient and public involvement

During the design and conduct of the study, we involved two ex-ICU patients as patient-perspective representatives. The primary research question, its outcome measures and the burden of the intervention have been assessed and found relevant by these patient-representatives. The role and tasks of the patient-representatives for the study have been detailed as (1) to help select meaningful assessment tools of patient and family experiences during and after ICU stay; (2) act as liaison between the study management team and the Dutch foundation ‘Family and patient Centred Intensive Care’ (FCIC; one representative is a formal representative for FCIC); (3) act as members of the Stakeholders group to provide advice on the study contents, execution and course on a regular basis to ensure the patient and family perspective; (4) advise on the contents of the patient information form and the informed consent procedure; (5) advise on ways to minimise loss to follow-up for the functional and cognitive outcome assessments; (6) advise on contents and organisation of symposia during the study on delirium and its consequences with the aim to better inform participants of the study and their family members and maximise their involvement; and (7) advise on the contents of the supporting website of the trial. Study participants will be informed about the most important results of the trial, either by post or symposium, when they indicate this on the informed consent letter.

## Ethics and dissemination

The study has been approved by the Medical Ethics Committee of the Erasmus University Medical Centre Rotterdam (MEC2017-511) and the Institutional Review Boards of participating sites. The study will be conducted according to the principles of the Declaration of Helsinki (version, date, see for the most recent version: www.wma.net) and in accordance with the Medical Research Involving Human Subjects Act (WMO) and other guidelines, regulations and Acts.

### Recruitment and consent

Recruitment of eligible patients will be done at admission. Informed consent for *possible* participation (ie, only when participants develop delirium at the ICU) will be obtained from subjects who are not expected to leave the ICU within the first 24 hours after admission and are not yet delirious. Informed consent will be obtained from the patient or (if the patient is unable to consent) from the patient’s representative. This procedure of prior request for informed consent will facilitate randomisation when the patient indeed develops delirium because randomisation can then be performed 24/7 since informed consent is already obtained and delirium often surfaces during the evening and night when obtaining informed consent is difficult. The informed consent procedure will be clearly delineated from the randomisation procedure. Importantly, when a patient with prior informed consent develops delirium and can thus be randomised, still a pre-randomisation check with regard to inclusion and exclusion criteria will be performed to confirm that the patient fulfils the inclusion, and not the exclusion criteria (because this may change over time). A team of dedicated research and ICU nurses and physicians (local principal investigator (PI), PhD student, PI, post-doc) will be trained to perform the informed consent procedures and help with the randomisations. Moreover, a 24/7 study consultation telephone number will be opened to help with problems or question during the study. A second type of randomisation concerns patients who are delirious at admission to ICU. These patients’ next-of-kin will be asked to grant permission to participate by means of informed consent when they are legally representative for the patients and the patient has no contraindications. After informed consent is obtained, the patient can be randomised.
